### Study assessment visits

Symptom severity ratings are performed at weeks 1, 2, 4, and 6 post-randomization. At each of these visits, participants complete the PSS-SR, and QIDS-SR to assess PTSD and depressive symptom severity, respectively. A qualified rater administers the CAPS (for the past week), MADRS, and C-SSRS and all subjects also meet with a study psychiatrist for assessment of CGIs, concomitant medications, and adverse events. Additional self-report measures repeated at the week 6 post-randomization visit include the BPI, PSQI, LES and SDS. Vital signs are assessed at each visit and laboratory testing, particularly for liver enzyme changes, is conducted throughout the trial according to the schedule in Table 1. Side effect burden is assessed through physician inquiry and patient completion of the PRISE and the Frequency, Intensity, and Burden of Side Effects Rating (FIBSER) [42].

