### Major endpoints

The primary outcome is mean change on the CAPS past-week score between the two treatment arms. Secondary outcomes include response and remission on the CAPS past-week score. Response is defined as ≥ 50% reduction from the baseline CAPS total score at the final on-drug study visit (V9 for completers). Remission is defined as a CAPS score ≤ 20 at the final on-drug visit.

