### Data analyses

#### Primary aim

##### Primary analysis

Our primary statistical analysis plan will be performed under the intent-to-treat (ITT) principle that utilizes a likelihood-based, mixed effects model that assumes any missing data meet the missing at random (MAR) assumption. Continuous variables will be fit using SAS PROC MIXED (SAS Institute Inc., Cary, NC, USA), and categorical data will be fit using the gllamm add-on to Stata [45]. Prior to model fitting, we will examine the distributions of the continuous outcome variables using visual inspection of histograms and boxplots to identify potential outliers. If variables are not normally distributed or contain outliers, then log transformations will be considered or appropriate nonparametric procedures will be substituted for the analyses stated. To address the possible increase in Type I errors due to multiple outcome variables, we have *a priori* selected a single outcome measure (CAPS total for past week) which will maintain the significance level (α) 0.05 for the primary analysis. For secondary outcome measures, we will adjust *P*-values by controlling for the false discovery rate [46] and report both unadjusted and adjusted *P*-values.

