#### Secondary aims

##### Response rates

We will use a mixed effects model for the binary response data (generalized linear mixed model or GLMM) where, at each time point, a subject will be classified as a responder if there is at least 50% improvement in CAPS compared to the baseline measure. The factors in the model will be the same as for testing the primary hypothesis above. This analysis is an averaged group comparison of time-point specific response rates, and thus a patient can change response categories over time. We anticipate observing a significant group-by-time interaction and will perform *post hoc* tests by time point to estimate when a significant divergence in response rates occurs.

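### Response is defined once per patient at the final on-drug visit, but the only stated analysis averages visit-by-visit response, so the analysis does not estimate the endpoint

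*Protocol article*

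**What the plan says.** **Endpoint (Major endpoints).** Response and remission on the past-week CAPS are the secondary outcomes named there. Response is a 50% or greater "reduction from the baseline CAPS total score at the final on-drug study visit (V9 for completers". Remission is a CAPS score of 20 or below "at the final on-drug visit". Each patient therefore has one status. For anyone who stops before Visit 9, it comes from an earlier visit.

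**Analysis (Secondary aims, Response rates).** The model is a generalized linear mixed model in which, "at each time point, a subject will be classified as a responder if there is at least 50% improvement in CAPS compared to the baseline" value. The section explains: "This analysis is an averaged group comparison of time-point specific response rates, and thus a patient can change response categories over time". It expects a group-by-time interaction and adds post hoc "tests by time point to estimate when a significant divergence in response rates occurs". On model terms it says only: "The factors in the model will be the same as for testing the primary hypothesis above".

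**Context.** Study assessment visits gives the on-drug rating times: "Symptom severity ratings are performed at weeks 1, 2, 4, and 6 post-randomization". Primary analysis sets the general approach, a likelihood-based "mixed effects model that assumes any missing data meet the missing at random (MAR) assumption". Statistical power/sample size expects 35% dropout.

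**The concern.** A single status at the end of treatment and a changing status averaged over visits are different quantities. The article states both the definition and the model, so the mismatch does not come from condensing a longer document. No sentence says which output of the model is the test of the response endpoint.

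Two consequences follow. First, an analyst who follows Response rates to the letter reports a visit average, which says little about where patients stand at the end of treatment if the effect changes over time. Second, an analyst who follows Major endpoints classifies early stoppers on an earlier value. In effect this carries that value forward, which is not how the mixed model treats missing visits under MAR. With both routes open, the choice could be made after the results are seen.

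**Working it through.** **1. How many patients the two rules treat differently.** Inputs from Statistical power/sample size: 50 completers per group and 35% dropout.

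- Plan's own figure: 50 / (1 − 0.35) = 76.9, so 77 per group and 154 in total. This reproduces the stated numbers.
- Expected early stoppers: 77 − 50 = 27 per arm, 54 of 154 overall (35%).

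By the Major endpoints rule, these patients are classified at their last on-drug rating (Week 1, 2 or 4 on the stated schedule). In the mixed model, their later visits are missing and handled under MAR.

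**2. How far the quantities can separate.** The article gives no response rates, so these are assumptions: placebo response of 5, 10, 20 and 30% at Weeks 1, 2, 4 and 6; in each arm 9 early stoppers last rated at each of Weeks 1, 2 and 4; and stoppers responding at their arm's rate for that week. With visit differences d1, d2, d4 and d6:

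- visit average = (d1 + d2 + d4 + d6) / 4
- final on-drug visit = (9·d1 + 9·d2 + 9·d4 + 50·d6) / 77

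| Assumed drug response (%), Weeks 1/2/4/6 | Differences (points) | Week 6 | Final on-drug visit | Visit average |
|---|---|---|---|---|
| Late divergence: 5/12/30/50 | 0, 2, 10, 20 | 20 | 1108/77 = 14.4 | 32/4 = 8.0 |
| Steady divergence: 8/17/33/50 | 3, 7, 13, 20 | 20 | 1207/77 = 15.7 | 43/4 = 10.75 |
| Early, fading effect: 20/30/35/35 | 15, 20, 15, 5 | 5 | 700/77 = 9.1 | 55/4 = 13.75 |

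The average is about half the Week 6 difference or less in the first case, and nearly three times as large in the third.

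**3. When last-on-drug-visit status distorts the comparison.** Assume true Week 6 response of 50% in both arms and 10% response at the last visit among early stoppers. Arm rate = (1 − dropout) × 0.50 + dropout × 0.10.

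- Dropout 35% in both arms: 0.36 against 0.36, no difference.
- Dropout 30% against 40%: 0.38 against 0.34, a 4-point difference with no Week 6 effect. If stoppers respond at 20%, it is 0.41 against 0.38, or 3 points.

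In this null case the distortion appears only when dropout differs by arm. A difference in the timing of dropout can act the same way.

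**The case against.** The strongest reply is that the plan offers more than an average. The model has a group-by-time interaction and tests at each time point, so a Week 6 contrast comes out of the same fit. For patients who reach Visit 9, Week 6 status and the defined endpoint coincide. This is right as far as it goes. But those tests are labelled post hoc and are meant to find when the groups diverge, the Week 6 contrast is never named as the result, and for early stoppers it still differs from the defined status.

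A second reply is that status at the last on-drug visit is a recognisable while-on-treatment choice, that the article expects a single dropout rate, and that it never states a test of that status. This stands against any claim that the planned results are biased by carrying values forward. The article does not use that term, and the distortion in the null example needs unequal dropout. What remains is that the definition and the model treat early stoppers differently.

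A reader might infer three further faults that the text does not support:

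- **Complete separation in the response model, because nobody can respond at baseline.** This assumes that the model has a pre/post time factor. That structure appears only in the power calculation; Primary analysis lists no factors, and nothing puts a baseline row into the binary model.
- **Averaging always dilutes the effect.** The fading-effect case shows the reverse.
- **The same mismatch for remission.** No remission model is stated, and that detail may sit in the full plan, so there is nothing for the definition to contradict.

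**Conclusion.** The point holds for response: the stated analysis does not estimate the stated endpoint, and the article does not say which contrast is the result. It rests on the text of two sections and needs no assumption about data. Its size does depend on assumptions. With the illustrative curves, the visit average lies between 12 points below and 8.75 points above the Week 6 difference, depending on the time course. About 27 of 77 patients per arm would have their status set by an earlier visit. A distortion of 3 to 4 points from last-visit status is conditional on dropout of 30% against 40% and on a test that the article does not specify.

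The primary outcome, its significance level and the sample size are unaffected. The change should be made, but it concerns secondary results only.

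**What to change.** 1. In Major endpoints, define response at Week 6 (Visit 9), and define remission at the same visit for consistency.
2. In Response rates, fit the model to post-baseline visits and name the Week 6 group contrast as the secondary response result. Report it as a difference in marginal response probabilities with a 95% CI. With a logit link, the model's direct output is a subject-specific odds ratio, so the probabilities need to be standardised over the trial population.
3. Label the visit average and the last-on-drug-visit status as supportive or sensitivity analyses, and say how each handles early stoppers.

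The cost is wording in two paragraphs and one standardisation step. No visits, ratings or patients are added.

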### Data management

Case report forms are adaptations of NIMH and industry-funded clinical trial protocols in PTSD. Study data is recorded on paper forms and entered into a password-protected relational database (Microsoft Office Access 2010, Microsoft, Redmond, WA, USA). A local area network resident relational database (Microsoft Office Access 2010, Microsoft, Redmond, WA, USA) serves as the secure repository for study data. Database management is performed by the study biostatistician.

### Data analyses

#### Primary aim

##### Primary analysis

Our primary statistical analysis plan will be performed under the intent-to-treat (ITT) principle that utilizes a likelihood-based, mixed effects model that assumes any missing data meet the missing at random (MAR) assumption. Continuous variables will be fit using SAS PROC MIXED (SAS Institute Inc., Cary, NC, USA), and categorical data will be fit using the gllamm add-on to Stata [45]. Prior to model fitting, we will examine the distributions of the continuous outcome variables using visual inspection of histograms and boxplots to identify potential outliers. If variables are not normally distributed or contain outliers, then log transformations will be considered or appropriate nonparametric procedures will be substituted for the analyses stated. To address the possible increase in Type I errors due to multiple outcome variables, we have *a priori* selected a single outcome measure (CAPS total for past week) which will maintain the significance level (α) 0.05 for the primary analysis. For secondary outcome measures, we will adjust *P*-values by controlling for the false discovery rate [46] and report both unadjusted and adjusted *P*-values.

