Because many patients with PTSD have experienced multiple traumas over their lifetime, it is necessary to identify the ‘index’ trauma, defined as the trauma currently causing the greatest distress or impairment to the patient. To identify the index trauma, participants complete Parts 1 and 2 of the Posttraumatic Diagnostic Scale (PDS) [25] at the screening visit. Part 1 is a short checklist of 12 items that identifies potentially traumatizing events the patient has experienced, and Part 2 asks which of these events has troubled them most in the last month. After confirmation with the study clinician, the trauma identified in Part 2 is determined to be the primary trauma and used as the focus of the Clinician-Administered PTSD Scale (CAPS) [26], to monitor PTSD symptom severity and change throughout the trial. The CAPS is a 17-item scale that assesses each of the 17 DSM-IV PTSD symptom diagnostic criteria. Each symptom is scored separately for both its frequency and intensity. Frequency ratings are made on a 5-point scale (0 = never; 4 = daily or all the time). Symptom intensity ratings are made on a 5-point scale (0 = none or no problem with symptoms; 4 = extreme, incapacitating). The total CAPS score is the sum of the frequency and intensity scores for each item. At the screening and baseline (that is Visit 3) visits, the CAPS is scored separately for symptoms present for the past week and for the past month. Subjects must score ≥ 50 for both the past week and the past month at the screening and baseline visits to remain eligible for the study. After baseline, the CAPS is assessed only for the past week of symptoms, except for the final visit (Visit 11, one month after last dose of study medicine), when past week and past month are both scored.

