### Randomization

Randomization occurs at Visit 3. To prevent confounding of the biological measures by the dexamethasone dose on the night before Visit 3, baseline laboratory and ECG tests are conducted the day prior at Visit 2. At Visit 3, upon completion of the post-dexamethasone venipuncture, participants are assessed with the CAPS, MADRS, C-SSRS, and CGI-S. To be eligible for randomization, participants have to score ≥ 50 on the CAPS rating for both the past week and the past month at this visit. At this visit subjects also complete the PSS-SR, QIDS-SR, the Pittsburgh Sleep Quality Index (PSQI) [40], Brief Pain Inventory (BPI) [41], and Patient Rated Inventory of Side Effects (PRISE) [42]. Self-reported functioning is assessed using the Sheehan Disability Scale (SDS) [43]. To assess the impact of recent significant life events, participants also complete the Life Experiences Survey (LES) [44].

Participants who meet all inclusion and no exclusion criteria are eligible for randomization. Treatment assignment lists, generated using randomized permuted blocks for each site, are used at each site to ensure equal allocation across treatment groups across the sites and at any time during the study. These lists were individually printed, placed in sealed opaque envelopes by the study biostatistician, and then delivered directly to the Investigational Drug Pharmacy personnel at each site. When a participant completes all procedures necessary for randomization, the study physician at each site notifies the pharmacy personnel, who assign the patient to the treatment group indicated on the randomization list.

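### The primary CAPS analysis can be replaced after a visual look at the data, on an outlier trigger that is easily met, by methods that do not estimate the mean change the trial defines and powers.

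*Protocol article*

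**What the plan says.** All places are in the protocol article.

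- **Major endpoints** defines the target: "The primary outcome is mean change on the CAPS past-week score between the two treatment arms".
- **Statistical power/sample size** sizes the trial on a difference of seven CAPS points, with 50 completers per group and 35% expected dropout.
- **Primary analysis** specifies an intention-to-treat analysis by a "likelihood-based, mixed effects model that assumes any missing data meet the missing at random (MAR) assumption". It then adds a data-dependent rule. "Prior to model fitting, we will examine the distributions of the continuous outcome variables", and the means is "visual inspection of histograms and boxplots to identify potential outliers". If a variable is judged non-normal, or has outliers, "log transformations will be considered or appropriate nonparametric procedures will be substituted for the analyses stated".

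The rule stands under the primary-analysis heading and covers continuous outcomes generally, with no exception for CAPS. It does not define an outlier, name the nonparametric procedure, rank the two alternatives, or say whether the inspection pools the arms.

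**The concern.** A primary analysis should be fixed before anyone sees outcome data. Here the document itself provides for replacing it, so this is not detail left to an analysis plan that is not shown. Three things are at stake.

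1. **Target.** The replacements do not estimate the mean difference in CAPS points that the trial defines and powers.
2. **Missing data.** A simple two-sample rank test at Week 6 does not carry the likelihood-based handling of missing data, in a trial that expects 35% dropout.
3. **Freedom of choice.** The trigger is judged by eye and the replacement is open. If arm or result informs the choice, the nominal 5% level is not protected.

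The check is also aimed at the wrong object. The mixed model assumes normality of residuals and random effects, not of the raw histogram of the outcome.

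**Working it through.** **Plan's own figure.** 50 / (1 − 0.35) = 76.9, rounded up to 77 per group, 154 in total. This reproduces the stated sample size. The stated power of 0.91 cannot be checked because the SD is not given as a number; with a two-sided 0.05 test it implies an SD of change of about 10.6.

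**How easily the outlier trigger is met.** Assumption: the usual boxplot rule (beyond the quartiles by more than 1.5 × IQR) applied to exactly normal data.

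- Fence in SD units: 0.6745 + 1.5 × 1.349 = 2.698. Probability that one observation falls outside: about 0.0070.
- With population quartiles, P(at least one) = 1 − (1 − 0.0070)^N, about 50% for N = 100 and 66% for N = 154.
- With sample quartiles, as a boxplot uses them, simulation gives 56% for N = 100 (the planned completers) and 67% for N = 154.
- CAPS is rated at baseline and weeks 1, 2, 4 and 6, so there are five distributions. With an assumed between-visit correlation of 0.6, the chance of an outlier at one or more visits is 97% (N = 100) to 99.5% (N = 154). The limits are the single-variable 56–67% if visits were perfectly correlated, and 1 − 0.44^5 = 98.4% to 1 − 0.33^5 = 99.6% if independent.

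Data that satisfy the normal assumption perfectly would thus usually meet the written condition.

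**What the replacements estimate.**

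- *Log scale.* Seven points is 53 against 60, a ratio of 53/60 = 0.88, but 33 against 40, a ratio of 33/40 = 0.83. A constant point difference is not a constant ratio. CAPS items start at 0, so a total of 0 has no logarithm without an offset, and neither does a negative change score. In one assumed scenario (SD of change 19), log(CAPS + 1) moved endpoint skewness from 0.17 to −2.5, so it made the shape worse.
- *Rank test.* It addresses whether values in one arm tend to be lower, not the mean difference in points. A two-sample test on Week 6 completers would use about 100 of 154 patients.

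**Type I error.** Assumed null scenarios, 50 per arm, candidates being a t test on raw change, a t test on the log(CAPS + 1) scale, and a rank test:

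| Scenario | Each test alone | Smallest of three p-values |
|---|---|---|
| Latent baseline mean 70, SD 20, truncated at 50; endpoint = 0.5 × baseline + N(0, 20), floored at 0; 5,000 runs | 5.5%, 4.8%, 5.1% | 9.6% (6.3% for t and rank only) |
| Latent baseline mean 70, SD 16, truncated at 50; SD of change 19; 20,000 runs | 4.9%, 4.6%, 4.7% | 7.8% |

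A mechanical switch on pooled change scores, blind to arm, gave 4.5% in the second scenario. The switch fired in only about 4.5% of those runs, so that figure alone is weak evidence. The general argument is stronger: if arms are exchangeable under the null, a choice that depends only on the pooled values leaves the level of each test essentially intact.

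**The case against.** **The order of steps limits the harm.** Inspection precedes model fitting, so no p-value need be in view when the method is chosen, and log transformation is only to be considered. This stands. The 8–10% figures describe picking the best result, which the article does not propose.

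**A reader might infer that the claim to hold alpha at 0.05 is false.** The article does not support that. The sentence addresses multiplicity of outcome variables, not choice of model, and inflation depends on how the inspection is done.

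**A reader might infer that the CAPS entry threshold all but forces the trigger**, since patients must score at least 50 "for both the past week and the past month at the screening and baseline visits to remain eligible for the study". That rule truncates only the screening and baseline scores, and the article gives no CAPS mean, SD or shape. Over assumed latent baselines (means 60 to 85, SDs 12 to 20), a Shapiro-Wilk test at N = 154 flags baseline in 6% to 100% of trials. In one such scenario it flagged baseline in 74% of trials and the change score in 4.5%, which is chance level. The entry rule should not be used as an argument.

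**A rank procedure need not drop early terminators.** No test is named, and the response definition already uses a final on-drug visit. True, but a last available value is a different treatment of missing data from the stated likelihood model. The loss of about 54 patients is therefore one possible outcome, not a certain one.

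**The study biostatistician's two roles.** Allocation lists were "placed in sealed opaque envelopes by the study biostatistician", and "Database management is performed by the study biostatistician". A reader might infer an unblinded choice of analysis. The article does not say that allocation is held in the database or that distributions are viewed by arm. This is only a reason to state the blinding explicitly.

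**An analyst may disregard a stray boxplot point.** Quite possibly, but the rule as written does not tell them to, and that discretion is part of the difficulty.

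**Conclusion.** The concern holds in limited form. Followed as written, the rule can replace the primary mixed model with an analysis that does not estimate the mean CAPS change the trial defines and powers. The outlier condition is likely to be met even when nothing is wrong: 56–67% for one variable and 97% or more over five visits, assuming normal data, the 1.5 × IQR rule and, for the visits, a correlation of 0.6. The damage to the target of estimation does not depend on any simulation and remains even if the inspection is fully blinded.

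Inflated type I error is conditional: roughly 8–10% if the best of three results is chosen, in scenarios whose CAPS distributions are assumed, and about the nominal level or slightly below if the switch is mechanical and pooled. The article does not say which applies, so neither inflation nor its absence can be asserted.

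**What to change.** - Exempt the primary outcome from the substitution rule. State that the likelihood-based mixed model on untransformed CAPS past-week score is the sole primary analysis.
- Check model residuals instead of raw outcome histograms, and say that the check does not change the primary analysis.
- Report log-scale, rank-based or robust-standard-error analyses only as labelled sensitivity analyses.
- State that outlier and data-cleaning decisions are made blind to allocation.

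The cost is wording and slightly more analysis work. If residuals prove markedly skewed there may be a small loss of efficiency. In the assumed scenario with SD of change 19, there was none: power for seven points with 50 per arm was 0.44 raw, 0.42 rank and 0.33 log. These are useful only relative to each other, because the SD is assumed. The change should be made before unblinding.
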